**Figure 4 fig04:**
[figure not shown]
Overview of the GIDEON safety, efficacy, treatment and baseline patient assessments and end-points

**Figure 3 fig03:**
[figure not shown]
GIDEON patient assessment schedule

The population of patients who entered this study and received at least one dose of sorafenib will be valid for intent-to-treat safety and efficacy analysis. However, patients who received sorafenib in the past will be excluded from efficacy analysis. All baseline demographic data will be summarised for the intent-to-treat population. AEs and other safety parameters, including blood pressure, Child-Pugh grade and Eastern Cooperative Oncology Group performance status (ECOG PS), will be summarised using the safety population.

Planned subgroup analyses conducted globally, regionally and by country will include: the impact of baseline characteristics on safety, particularly Child-Pugh B; the relationship between baseline characteristics and efficacy; the duration of sorafenib therapy and reasons for discontinuation; the effect of other treatments for HCC on outcome and the impact of different practice patterns on outcome. In addition, subgroup analyses for specific regions may be conducted, such as: an evaluation of common treatments for HCC in Asia; referral and diagnostic patterns in Europe; duration of treatment, tolerability and compliance in Latin America and patient selection for loco-regional therapy in Japan. However, all subgroup analyses performed will depend on the actual data collected.

### Statistical considerations for GIDEON

An overall sample size of 3000 patients with unresectable HCC treated with sorafenib is expected to be sufficient to allow for evaluation of safety of the overall population as well as specific subgroups. With this sample size, there would be an 84% chance of observing an AE with a true incidence of 1% in at least 25 patients.

All baseline, safety and efficacy data were analysed using descriptive statistics. Kaplan–Meier estimates were calculated for the OS, PFS and TTP efficacy end-points. At the time of the analyses, any patient alive or lost to follow-up, without disease progression or death or without documented radiological progression will be censored at the last date of evaluation for OS, PFS and TTP analyses, respectively. Exploratory subgroup analyses of efficacy and safety data may also be performed, stratified by prognostic/predictive baseline factors such as stage, Child-Pugh score, ECOG PS, region and age, as appropriate. Data regarding administration of sorafenib such as duration, given dose, continuation or discontinuation of therapy and dose modification of sorafenib therapy, including reason(s) for discontinuation, will be summarised in a descriptive manner. Treatments for HCC other than sorafenib before, during and after therapy with sorafenib will be summarised descriptively as per available data. The sample size was calculated to collect data to allow for sufficient evaluation of safety monitoring of all treated patients. Interim analyses are planned during the study primarily for summarising and monitoring safety data, and will be conducted after 500 patients and 1500 patients are enrolled and have been treated on study for at least 4 months.

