## The GIDEON study

### Aims, objectives and rationale for GIDEON

Non-interventional studies, or observational studies, are postauthorisation safety studies (PASS) that are usually conducted to gain further information about a licensed product. Observational studies are characterised by the fact that assignment to a particular therapy strategy is not mandated by a study protocol but reflects the participating physician’s current practice. The physician alone decides which treatment, if any, is appropriate. In NIS, the decision to include a patient in a study is separate from the treatment decision. Furthermore, no additional diagnostic or monitoring interventions are mandated for the patient as a result of inclusion in an NIS. NIS serve a wide range of purposes but are of particular value in providing information in wider populations or subgroups not covered in RCTs (14). NIS also enable information to be gathered on other parameters not usually assessed in the clinical trial setting, such as patient acceptance and compliance, physician adherence to information and directions for use and prescription behaviour. The importance of NIS in the literature is increasingly recognised, and guidelines were developed to improve the analysis and reporting of observational studies (15). NIS provide opportunities to enhance the evidence base for established drugs and therapies and increase understanding of the impact of treatments in real-world practice (14).

GIDEON is a global, prospective NIS of patients with unresectable HCC who are candidates for systemic therapy and for whom the decision has been taken to treat with sorafenib. It was initiated to fulfil the postapproval commitment to organisations such as the European Medicines Agency to gather data on the safety and efficacy of sorafenib in patients with Child-Pugh B liver function. Additional goals are to compile a large and robust database of HCC treatment patterns and outcomes among patients with unresectable disease who are candidates for systemic therapy, to answer clinically relevant questions and gain a better understanding of the safety of sorafenib with loco-regional therapies, given either concomitantly or sequentially. Data will also be gathered in the USA and possibly other regions on the characteristics, disease course and treatment outcomes of patients with newly diagnosed HCC or recurring disease after curative treatments, who are not candidates for systemic therapy with sorafenib.

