Based on these goals, the primary objective of GIDEON is to evaluate the safety of sorafenib in patients with unresectable HCC in real-life practice conditions. Secondary objectives are to: evaluate the efficacy [OS, progression-free survival (PFS), time to progression (TTP), response rate and stable disease rate] of sorafenib in these patients; determine the duration of therapy according to various patient characteristics; evaluate methods of patient evaluation, diagnosis and follow-up; assess comorbidities and their influence on treatment and outcome in real-life practice rather than a controlled clinical trial setting and evaluate the practice patterns of the physicians involved in the care of these patients.

This study was conducted according to established regulations and recommendations relating to the conduct of NIS; volume 9A of the Rules Governing Medicinal Products in the European Union (16). When required, documented approval from the appropriate ethics committee(s)/institutional review board was obtained for all participating centres prior to the study, according to Good Clinical Practice and local laws, regulations and organisations.

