### Patients to be included in GIDEON

Patients with histologically or cytologically documented or radiographically diagnosed unresectable HCC who are candidates for systemic therapy, and for whom a decision has been made to treat with sorafenib, are eligible for inclusion in GIDEON if they have a life expectancy of > 8 weeks and have provided signed informed consent. Patient exclusion criteria are based on the approved local product information for sorafenib.

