### What are the limitations of GIDEON?

The information gathered in GIDEON will form a large and robust database that will be analysed to improve our understanding of the global, regional and local differences in patient demographics, disease course and treatment outcomes, with a view to improve our knowledge base and improve patient outcomes. However, as this is an observational NIS, it is associated with a number of limitations. The lack of randomisation to specific treatment arms and the lack of a placebo-control arm will limit any robust evaluation of the efficacy of any of the treatments received by these patients during the course of the study. Comparisons between sorafenib-treated and untreated patients in the USA will be limited because of the small sample size of patients in the USA who will not receive sorafenib. The value of some subgroup analyses may also be limited by small patient numbers, although these analyses may still be hypothesis-generating and could help direct future research. However, given these limitations, it will be important to consider findings from GIDEON together with emerging data from large RCTs, to fully evaluate the safety and efficacy of these treatments and draw any definitive conclusions.

Another possible limitation in GIDEON is that all data will be collected via the completion and submission of CRFs, which could delay data collection and evaluation. However, electronic versions of the CRF have been compiled with a view to facilitate this process and to reduce any lengthy delays in completing and analysing the data collected.

As with any observational study, a number of biases may also exist. The lack of blinding of either the treating physician or the patient to study treatment may introduce a bias in reporting treatment outcomes. It is also possible that physicians engaged in GIDEON may be more likely to choose sorafenib therapy for a larger proportion of their patients than would be representative of normal treatment practice patterns in that area, although all patients receiving sorafenib therapy must be eligible according to the locally approved product information for sorafenib. Finally, while study procedures regarding data collection and verification are in place for GIDEON, it should be noted that in an NIS, potential exists for less robust data than might be expected from an RCT.

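### Questions worded as influence, impact and effect are paired with a wholly descriptive analysis, and the limitation on the US treated-versus-untreated contrast gives small numbers but not the difference in candidacy.

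*Protocol article*

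**What the plan says.** **Analysis.** Under Statistical considerations for GIDEON, the article states that "All baseline, safety and efficacy data were analysed using descriptive statistics". Kaplan–Meier estimates are given for OS, PFS and TTP, and HCC treatments other than sorafenib are summarised descriptively. Exploratory subgroup analyses are optional, "stratified by prognostic/predictive baseline factors such as stage, Child-Pugh score, ECOG PS, region and age, as appropriate". No regression, weighting or other adjustment is named.

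**Questions.** One secondary objective is to "assess comorbidities and their influence on treatment and outcome in real-life practice" (Aims, objectives and rationale for GIDEON). The planned subgroup analyses at the end of Data collection cover the impact of baseline characteristics on safety, particularly in Child-Pugh B, the effect of other HCC treatments on outcome, and the impact of practice patterns on outcome. The Abstract says that ethnicity, stage, comorbidities and tumour morphology all affect outcome and differ between regions. On eligibility, "Patient exclusion criteria are based on the approved local product information for sorafenib".

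**US cohort.** Treated patients must be candidates for systemic therapy for whom a decision to give sorafenib has been made (Patients to be included in GIDEON). The additional cohort, in the USA and possibly elsewhere, has newly diagnosed disease or recurrence after curative treatment and consists of patients "who are not candidates for systemic therapy with sorafenib" (Aims, objectives and rationale for GIDEON). The limitations section says: "Comparisons between sorafenib-treated and untreated patients in the USA will be limited because of the small sample size of patients in the USA". The small group meant there is the untreated one.

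**The concern.** A descriptive analysis answers how often and how long. It does not answer whether a comorbidity, a practice pattern or another treatment is itself related to outcome once the patients' other characteristics are taken into account. The article recognises that prognostic factors move together across regions, so a crude contrast between any two groups can carry the difference in case mix as well as the factor of interest. At stake are the conclusions that the Discussion hopes to support: a staging classification usable worldwide and a treatment algorithm.

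The US limitation is a separate matter. Naming only small numbers invites the reader to think that more untreated patients would make the contrast informative. They would only narrow the interval around an estimate that compares candidates with non-candidates.

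**Working it through.** **1. The plan's own figure.** The only numerical design statement is "An overall sample size of 3000 patients with unresectable HCC treated with sorafenib" with the claim that "there would be an 84% chance of observing an AE with a true incidence of 1% in at least 25 patients". Exact binomial: P(X ≥ 25 | n = 3000, p = 0.01) = 0.844. The figure reproduces. It concerns detecting an adverse event in the whole population and says nothing about contrasts between groups, so nothing below depends on it.

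**2. How far a crude contrast can drift.** The documents give no prevalence of any prognostic factor by group and no strength of its association with outcome. Every input in this step is therefore an assumption. Take two groups A and B with no true difference, and one binary factor that multiplies event risk by g, with prevalence pA and pB. Then

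crude ratio B/A = [1 + pB(g − 1)] / [1 + pA(g − 1)].

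| g | pA | pB | Crude ratio | Ratio with pA and pB exchanged |
|---|---|---|---|---|
| 1.5 | 0.30 | 0.50 | 1.25/1.15 = 1.09 | 0.92 |
| 2 | 0.30 | 0.60 | 1.60/1.30 = 1.23 | 0.81 |
| 3 | 0.20 | 0.60 | 2.20/1.40 = 1.57 | 0.64 |

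The sample size does not appear in the formula. With 3000 patients the wrong value is estimated more precisely, not corrected.

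**3. A survival version.** Assume exponential survival with a baseline median of 10.7 months (the sorafenib arm of the Western phase III trial cited in the Introduction), no Child-Pugh effect, and two independent factors: poor ECOG PS (hazard ratio 2.0) and advanced stage (hazard ratio 1.6). All inputs except the median are assumed.

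- Poor ECOG PS in 10% of A and 25% of B, stage not acting: crude hazard ratio about 1.08.
- Poor ECOG PS in 10% and 35%, with advanced stage in 45% of A and 60% of B: about 1.22.
- Poor ECOG PS in 10% and 25%, with stage reversed (60% of A, 45% of B): about 1.0.
- Poor ECOG PS in 10% and 35%, with stage 75% in A and 45% in B: about 1.0.

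Several imbalances may add up or cancel. Neither the direction nor the size can be known beforehand.

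**4. Could joint stratification do the work?** Stratifying by several factors at once is a form of adjustment. With assumed levels of 4 (stage) × 2 (Child-Pugh) × 3 (ECOG PS) × 4 (region) × 2 (age) there are 192 cells, and 3000/192 = 15.6 patients per cell on average, before comorbidity is added. Full cross-classification is impractical at that size.

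**5. The US contrast.**

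| | Treated | Untreated |
|---|---|---|
| Candidate for systemic therapy | Yes, required | No, by definition |
| Decision to give sorafenib | Yes, required | Not applicable |
| Reason given for limited comparison | — | Small numbers |

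The two entry definitions exclude each other on candidacy. The number of untreated patients affects precision only.

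**The case against.** The strongest reply is that this is a condensed article and that covariate sets and regression models belong in the full protocol or the SAP, which are not shown. That stands to this extent: a reader might infer that no adjusted analysis exists anywhere, and the article does not support that. But the article does more than stay silent. It states that all data are analysed descriptively, and that statement does not fit the questions it poses.

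A reader might also infer that factors are examined strictly one at a time. The text does not say so. It lists five stratification factors as examples, which leaves joint stratification open.

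A reader might infer that the Child-Pugh B commitment itself is undermined. It is not. The primary objective is safety in real-life use, and the commitment is to gather safety and efficacy data in Child-Pugh B. Event rates and survival within that group answer it without adjustment.

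Nor does the article hide its weaknesses. The limitations section names the lack of randomisation and of a placebo arm immediately before the US sentence, lists biases, regards subgroup results limited by small numbers as hypothesis-generating, and defers definitive conclusions to a joint reading with randomised trials.

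On the US cohort, a treated-versus-untreated comparison appears only as a limitation and not among the planned analyses. Small numbers are a real additional limit. Whether measured covariates overlap between the groups cannot be checked, so it would go too far to call any difference nothing but confounding by indication. What remains is that the reason attached to this contrast omits the difference in entry definition, which the general remark on randomisation does not disclose.

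Finally, local product information may make case mix differ by country, but no label content is given, so this is a possibility and not a demonstrated fact.

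**Conclusion.** The concern holds in a limited form. The stated analysis does not match the questions about influence, impact and effect, and adjusted estimates would answer them better at little cost. The bias in the crude contrasts may go either way. The illustrative range of 0.64 to 1.57 for one factor, and 1.0 to 1.22 for the survival examples, rests on assumed prevalences and effect sizes and is not an estimate for this study. The one part that needs no such assumption is that more patients do not reduce the bias.

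The US point is the firmest, because it follows from the article's own definitions: the groups differ in candidacy, so the contrast is confounded at any sample size, in addition to being small. Neither point affects the sample size statement or the descriptive safety results.

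**What to change.** 1. For the questions on comorbidities, baseline characteristics, practice patterns and other HCC treatments, report covariate-adjusted estimates with confidence intervals beside the crude ones. Use Cox models for OS and PFS and logistic or rate models for key adverse events, with Child-Pugh, ECOG PS, stage, age and comorbidity as covariates and region as stratum. If the full protocol or SAP already does this, bring the descriptive-only statement into line with it.
2. Word the results as associations.
3. Keep the descriptive rates within Child-Pugh B as they are.
4. In the limitations section, state that treated and untreated US patients differ by definition in candidacy for systemic therapy, so the comparison is confounded at any sample size as well as small. Describe the untreated cohort on its own and draw no treatment-effect conclusion from the contrast.

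The cost is wording and routine modelling. Child-Pugh, ECOG PS, stage, age and region are already named as baseline factors, and comorbidity is the subject of an objective. The main downside is that missing baseline values, to be expected in routine care, need a stated method, either complete-case analysis or imputation.

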## Discussion

### What will GIDEON achieve?

GIDEON is a global PASS initiated to collect more information on the safety and efficacy of sorafenib in patients with unresectable HCC. This is the largest prospective HCC NIS in the world, which will enrol 3000 patients from > 40 countries globally. The compilation of a database of this size in HCC has not previously been undertaken; as no other global registries exist in this area, it is anticipated that the data collected here will be an important contribution to our knowledge and will help to answer important and clinically relevant questions relating to the natural disease course of HCC and liver dysfunction, long-term efficacy and safety of sorafenib therapy, physicians’ practice patterns and patients’ perspectives.

The number of factors influencing HCC and its disease course make it extremely difficult to accurately assess patient prognosis and make optimum treatment recommendations. The geographical variation of these factors has also prevented the establishment of a universal system to assess all patients. Findings from GIDEON could help to establish a globally applicable staging classification, which could facilitate the accurate and consistent assessment of all patients and help to provide a common language for the broad HCC multidisciplinary team on which to base treatment recommendations. In addition, as GIDEON will collect data regarding the differences in physician treatment practice patterns and outcomes, it may be possible to analyse these data with a view to optimise the role of all members of this large multidisciplinary team and streamline patient care.

Although potentially curative therapy via surgical resection or transplant is possible for some patients with HCC, there is a lack of cadaveric transplants available, and the majority of patients are unsuitable for surgery at presentation. In addition, the recurrence rate of HCC after curative treatment is high and the long-term curable rate is low (17). Thus, non-surgical treatments play a central role in the management of these patients. However, there is still a relative shortage of RCTs to fully evaluate these treatments in all patient subgroups, and more work is needed to fully understand the benefits of each of these treatments and to establish their place in the HCC treatment armamentarium. One of the main focuses of GIDEON is to gain further information on the optimum duration of sorafenib therapy as well as the safety and efficacy of sorafenib in different subgroups of patients, especially patients who are generally excluded from RCTs to minimise errors or confounding factors in the study, i.e. patients who have moderate liver dysfunction (Child-Pugh B) where data are currently limited. However, information is also being gathered regarding the safety and outcomes following other treatments before, during and after sorafenib therapy; thus, it is anticipated that the information gathered in this study will help to improve our understanding of the risks and benefits associated with each of these treatment approaches, which could help us to establish an optimum treatment algorithm for these patients.

In addition to GIDEON, a large clinical trial programme for sorafenib is ongoing that should help us to fully establish its optimum place in therapy. One area of interest is the role of sorafenib as adjuvant therapy to improve survival of patients with HCC. To date, treatments such as radiotherapy and chemotherapy and their combination have been used to reduce tumour size and improve patients’ quality of life (18). TACE has recently been shown to be the only palliative treatment that can benefit HCC patients ineligible for curative treatments because of advanced tumour stage or poor hepatic functional reserve; however, the survival gain appears marginal (19) and other effective treatments are urgently needed. Against this background, a large Phase III, randomised, double-blind, placebo-controlled trial of adjuvant sorafenib following either surgical resection or local ablation is currently in progress (STORM study) (20). The primary end-point is recurrence-free survival, with secondary end-points including time to recurrence and OS. Estimated accrual to this trial is 1100 patients and data are due to be reported in 2014.

Another area of interest is the efficacy of sorafenib in combination with, and subsequent to, TACE therapy. A large randomised Phase II trial has been initiated to evaluate the role of sorafenib in combination with TACE in the treatment of patients with intermediate disease (SPACE study) (21). Estimated enrolment to this trial is 350 patients, and final results are expected in late 2010. In addition to this, a Phase III, double-blind, randomised, placebo-controlled trial of sorafenib following TACE in Japanese patients with unresectable, advanced disease is ongoing (Japan post-TACE study) (22). The target recruitment of 414 patients has already been reached and final results are anticipated in early 2010.

Finally, the effects of sorafenib in combination with other targeted agents in HCC are also of interest, and a large Phase III, randomised, double-blind trial evaluating the efficacy, safety and health-related quality of life of sorafenib plus erlotinib vs. sorafenib plus placebo for the first-line treatment of advanced HCC is in progress (SEARCH study) (23). The target recruitment for this study is 700 patients and the estimated final data collection date is July 2011.

These ongoing studies form a comprehensive and well-integrated clinical trial programme, which will provide data from several points in the treatment pathway. GIDEON is also a key component of this programme, as it will provide data from the entire unresectable patient population treated under real-life conditions, not in a non-restrictive setting and within the approved indication, and will enable the collection of data from populations not commonly included in RCTs, such as those with Child-Pugh B liver function. Thus, in addition to the ongoing interventional studies, the information collected in GIDEON will significantly contribute to the current body of evidence, which helps inform treatment decisions.

